## Abstract

**Background::**

In recent years, the role of vitamin D (VD) as a protective factor in cardiovascular disease has been recognized. Thus, there is a need to study the effect of vitamin D supplementation in the control of different cardiovascular risk factors and metabolic syndrome, especially in young populations where few studies have been conducted.

**Methods::**

Pilot study of a randomized, parallel two-arm, triple-blind clinical controlled trial in 150 adolescents and young adults in the city of Bucaramanga-Colombia. The intervention group will receive 1000 IU of VD and the control group 200 IU of VD daily for 15 weeks. The main outcomes are: serum calcifediol levels (25(OH) D), body mass index and lipid profile; secondary outcomes are complementary to the previous ones (skin folds, waist-hip ratio). Other variables will be analyzed such as assessment of dietary intake, physical activity, sun exposure, cigarette and tobacco consumption and compliance with VD supplementation.

**Discussion::**

This study is innovative since there is little evidence from clinical trials in adolescents and young adults; similar studies are not known in our context. The results of this study may facilitate the recommendation of oral vitamin D supplementation in the population of interest. In addition, it is a low-cost and easy-to-apply intervention that could contribute to the formulation and implementation of health policies.

**Trial registration::**

NCT04377386

## Introduction

1

The main and classic role of Vitamin D (VD) is the mineralization of the bone, regulating the activity of osteoblasts and facilitating the absorption of calcium and phosphorus from the intestines.^[1]^ Low VD levels have been associated to an increase in the incidence and mortality caused by chronic diseases such as cardiovascular diseases (CVD) among others, and their risk factors such as diabetes, obesity and dyslipidemia.^[2–4]^

These findings are clinically important because vitamin D deficiency (VDD) is favored by a sedentary lifestyle and excessive consumption of high-calorie foods, which in turn leads to obesity.^[5,6]^ Since this is a multifactorial condition, described as a phenotype of numerous pathologies, is one of the most serious public health concerns in the 21st Century and is not alien to the child and adolescent population.^[7]^

Specifically, obesity increases constantly in the child population becoming a threat by the risk of developing a number of chronic diseases in adult life, particularly CVD.^[8]^ It is estimated that more than 42 million children worldwide had overweight or obesity in 2016.^[9]^ Colombia is not alien to this problematic; by 2015, 24.4% of school children and 17.9% of adolescents had excess weight.^[10]^

Given this scenario, in 2006 a group of researchers in Bucaramanga, Colombia, set out to study the risk factors for metabolic syndrome (MS) in a group of children between 6 and 10 years of age and to initiate the SIMBA project (longitudinal study for the evaluation of cardio metabolic risk in young people in Bucaramanga).^[11,12]^ A prevalence of MS of 9.5% was determined on the baseline (95% CI: 8.0–11.3%)^[11]^ following the criteria of the Adult Treatment Panel III (ATP III) and 8.0% (95% CI: 6.6–9.7%) based on the International Diabetes Federation (IDF). Subsequently, the SIMBA II project was conducted between 2013 and 2017, which established a prevalence of MS of 13.1% and 14.8% according to ATP III and IDF, respectively; evidencing an increase in the prevalence of MS between 3.7% and 6.8% from school age to adolescence, in accordance with each criterion.^[13]^

Consequently, research has recently begun on the efficacy of VD supplementation in children. Thus, Rajakumar et al, found that the correction of VD levels in overweight and obese children, by administering vitamin D3 with 1000 or 2000 IU/day versus 600 IU/day, had no statistically significant effect on measures of arterial endothelial function or stiffness, systemic inflammation or lipid profile, however, they were able to evidence a reduction in blood pressure, glucose levels and improvement in insulin sensitivity, suggesting that optimization of the VD status of children can improve their cardiovascular health.^[14]^

Likewise, Marwaha et al, showed that VD supplementation with the three daily doses of vitamin D3 (600, 1000, and 2000 IU) lead to a significant increase on the serum levels of 25 (OH) D in school children with VDD and the secondary hyperparathyroidism decreased from 31.7% to 8.4% after supplementation.^[15]^

A significant aspect to consider in the vitamin D supplementation interventions is that they are low cost, easy to implement and very safe; consequently, if a positive effect is achieved, a problem of great impact and increasing prevalence, such as the metabolic syndrome and cardiovascular risk, would be intervened.

## Objective

2

To evaluate the efficacy of oral vitamin D supplementation in the reduction of the body mass index (BMI) and the lipid profile in adolescents and young adults of the SIMBA cohort in Bucaramanga, Colombia.

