## Methods

3

Design: Two-arm, triple-blind, parallel randomized controlled clinical trial.

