### Interventions

3.6

The intervention group will receive 1000 IU of VD and the control group 200 IU of VD daily for 15 weeks. All participants will be given 105 doses of VD. The supplementation will be provided by the laboratory *Farma de Colombia* and is commercially named as Farma D. Its commercial presentation is soft gelatin capsules.

The 75 participants assigned to the intervention group will take one (1) 1000 IU VD capsule daily for 15 weeks. The daily dose selected is based on the amount required for replenishment over a period of approximately 3 months, and is well below the intake levels associated with toxicity.^[16]^ On the other hand, the 75 participants in the control group will take 1 capsule of VD of 200 IU daily for 15 weeks, since the benefits of VD for the health of people have been demonstrated, this being the minimum recommended dose for children. The above, considering that it is unethical for the control group not to receive any type of supplementation.

The participants in both the intervention and the control group must record in a calendar the time of the daily intake of the supplement during the 15 weeks.

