## Discussion

4

The role of vitamin D as a protector against cardiovascular disease is widely recognized.^[2,3]^ For consideration, vitamin D supplementation is being widely studied to determine its effect on the control of cardiovascular risk factors and metabolic syndrome, including obesity, dyslipidemia, and impaired blood glucose.^[5]^

Studies on the effect of supplementation in adolescents and young adults are scarce; however, the favorable effect of supplementation in the serum levels of 25 (OH) D in school-age children with VDD and the reduction in blood pressure, the concentration of fasting glucose, and improvements in sensitivity to insulin in children with overweight and obesity is widely known.^[14,15]^ Notwithstanding this, more clinical trials are required to confirm these findings.

This research is innovative considering that there are few studies on adolescent and young adult populations and that these have not been carried out in Latin America.^[14,15]^ Consequently, if this trial provides positive results, it will be possible to recommend oral vitamin D supplementation for the reduction of BMI and lipid profile in the studied population. In addition, it is a low-cost and easy-to-apply intervention that could contribute to the formulation and implementation of health policies.

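### The objective and intended recommendation name vitamin D supplementation without dose or comparator, but both arms are supplemented and the trial estimates only 1000 versus 200 IU/day

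*Protocol article*

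**What the plan says.** The objective in section 2 of the protocol article reads: "To evaluate the efficacy of oral vitamin D supplementation in the reduction of the body mass index (BMI) and the lipid profile". The sentence goes on to name the cohort, but gives no dose and no comparator.

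The design, stated at the start of section 3, is a "Two-arm, triple-blind, parallel randomized controlled clinical trial". Section 3.6 defines the arms: "The intervention group will receive 1000 IU of VD and the control group 200 IU of VD daily for 15 weeks". The Abstract (Methods) and section 3.4 give the same two doses. Section 3.6 also explains why controls are supplemented. It describes the 200 IU capsule as chosen "since the benefits of VD for the health of people have been demonstrated, this being the minimum recommended dose for children", and holds that "it is unethical for the control group not to receive any type of supplementation".

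The intended conclusions are in two places. The Abstract (Discussion) says: "The results of this study may facilitate the recommendation of oral vitamin D supplementation in the population of interest". Section 4 says that, if results are positive, "it will be possible to recommend oral vitamin D supplementation for the reduction of BMI and lipid profile in the studied population". Neither names a dose or a comparator, and both go on to mention health policy.

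**The concern.** The objective and the foreseen recommendation are worded as a question about supplementation in general. The arms answer a different question: whether a higher daily dose does better than a lower one. Section 3.6 declines, on ethical grounds, to leave anyone unsupplemented, so no randomised comparison in the trial is against none.

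What is at stake is the conclusion. A reader who takes the objective at its word could read a null difference as showing that supplementation does nothing for BMI or lipids, although both arms may have changed. A positive difference could be read as the size of the benefit over no supplementation, which was not measured. A before-after change in the 1000 IU arm could be offered as an answer to the objective, because section 3.2 excludes current vitamin D users and the baseline is therefore an unsupplemented measurement.

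**Working it through.** The plan gives no figure on this point beyond the doses, so the check sets the passages side by side and writes down what the design estimates.

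**Inputs**
- Objective: supplementation, no dose, no comparator (section 2).
- Arms: two, at 1000 and 200 IU daily for 15 weeks (sections 3, 3.4 and 3.6; Abstract, Methods).
- Doses per participant: 105 (section 3.6).
- Intended recommendation: supplementation, no dose, no comparator (section 4; Abstract, Discussion).
- Tests named for outcomes: paired t, Wilcoxon and McNemar, with longitudinal methods to be explored (section 3.11).

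**1. The randomised contrast.** 1000 − 200 = 800 IU/day. Over the course this is 105 × 1000 = 105,000 IU against 105 × 200 = 21,000 IU, a difference of 84,000 IU.

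**2. What it estimates.** Let m(d) be the mean week-15 outcome under daily dose d. The trial estimates m(1000) − m(200). The effect of the higher dose against none is

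m(1000) − m(0) = [m(1000) − m(200)] + [m(200) − m(0)].

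The first bracket is randomised. The second is not, since no arm receives dose 0, and nothing in the trial's data recovers it.

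**3. How much the second bracket could matter.** The documents give no dose-response curve, so these are assumptions that show the range:
- 200 IU/day has no effect: the contrast equals 100% of the effect against none.
- Response proportional to dose: the contrast is 800/1000 = 80% of it, and 200/1000 = 20% is common to both arms.
- All of the effect is already reached at 200 IU/day: the contrast is 0%, although supplementation works.
- 200 IU/day is harmful for the outcome: the contrast exceeds the effect against none.

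**4. Reading a positive result.** If m(1000) is better than m(200), the evidence for the higher over the lower dose is direct. If 200 IU/day is not harmful for these outcomes, the second bracket is zero or points towards benefit, so the effect against none is at least as large as the contrast. This supports supplementation at the higher dose indirectly. It says nothing about 200 IU/day itself and does not give the size of the benefit over none.

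**5. Reading a null result.** Even with no sampling error, m(1000) = m(200) is compatible with no effect at either dose and with an equal effect at both. The objective as worded would be left unanswered.

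**6. Before-after changes.** The change within the 1000 IU arm is the effect of 1000 IU plus whatever would have happened anyway over 15 weeks (time, season, regression to the mean, taking part in a trial). With no unsupplemented arm, these parts cannot be separated. Comparing the changes between arms removes the common part, but what remains is m(1000) − m(200) again.

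**7. Consequence for other sections.** Section 3.3 already expresses the expected difference as one between the two arms. A corrected objective would agree with it, and no sample-size figure depends on this point.

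**The case against.** The comparator is not hidden. Both doses stand in the Abstract and in sections 3.4 and 3.6, with the reason for supplementing controls. Section 3.8 puts the Colombian dietary recommendation at 600 IU/day, so 200 IU/day is one third of it (200/600), and the control can be described as a low dose. Section 1 also speaks of the efficacy of supplementation when it introduces a cited trial in which every arm was supplemented. In this article the phrase need not imply an untreated comparator, and a one-sentence objective is made specific by the methods that follow.

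Much of this stands. There is no concealed design error, and a careful reader of section 3.6 will know what was compared. It does not rescue the recommendation, which carries no dose, or the objective, which a null result would leave unanswered. Nor can the control be treated as inactive on the document's own terms, because section 3.6 justifies it by the benefits of vitamin D.

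A reader might go further and infer that the trial could not support any recommendation to supplement. The documents do not bear that out. Section 4 makes the recommendation conditional on positive results, and step 4 above shows that such results would support the higher dose directly and supplementation indirectly. A reader might also infer that the Abstract and section 4 claim efficacy outright. That word appears in sections 1 and 2 but not in those two places, and the Abstract's sentence is hedged. Finally, no passage says that a null result will be read as failure of supplementation or that one arm's before-after change will be reported as its effect. These are possible misreadings. Whether paired tests suit a two-arm trial is a separate matter.

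**Conclusion.** The point holds as a mismatch between the stated objective and recommendation on one side and the randomised arms on the other. The trial estimates the between-arm effect of 1000 versus 200 IU/day over 15 weeks, a contrast of 800 IU/day, and nothing else about supplementation.

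The shortfall against the question as worded cannot be sized from the trial's data. On the assumptions above that 200 IU/day does no harm, the contrast could capture anything from none to all of the effect against no supplementation, with 80% under proportionality. The reading of a positive result as indirect support for supplementation also rests on the no-harm assumption. That a null difference leaves the objective unanswered, and that a one-arm change cannot show efficacy, follows from the absence of an unsupplemented arm and needs no assumption about the dose response.

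**What to change.** Reconcile section 2, section 4 and the Abstract (Discussion) with section 3.6:
- State the objective as the between-arm difference at week 15 in BMI and in the lipid measurements between the 1000 and 200 IU/day arms.
- Limit the conclusions in the Abstract and section 4 to that dose comparison, with both doses named. If support for supplementation against none is mentioned, call it indirect and state the assumption that 200 IU/day is not harmful for these outcomes.
- Add one sentence that a null difference between the arms is not evidence against supplementation as such, and that a before-after change within one arm will not be presented as efficacy.

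Arms, doses, sample size and procedures stay as they are. The cost is a narrower claim.

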## Methods

3

Design: Two-arm, triple-blind, parallel randomized controlled clinical trial.

### Population

3.1

The participants in the study are adolescents and young adults from the SIMBA cohort, initiated in year 2006 with a total of 1282 children between the ages of 6 and 10 years in the city of Bucaramanga, Colombia.^[11]^ Between 2013 and 2017 the SIMBA II project was carried out, which managed to contact and follow up 494 adolescents.^[13]^ Finally, in 2019, 217 participants were re-contacted by telephone. The latter constitute the population eligible for this study protocol (Fig. 1).

**Figure 1 F1:**
[figure not shown]
Population eligible.

### Eligibility criteria

3.2

Inclusion criteria

Belonging to the SIMBA cohort.Age ≥ 18 years.Re-contact consent from previous studies.

Exclusion criteria

Medical diagnosis of diabetes mellitus, clinically manifest endocrinopathies, acute or chronic infectious liver disease, and kidney disease.Adolescents or young adults subject to treatment with steroids or hormones (except levothyroxine) up to 1 month before lab sample taking.Current supplementation with VD (any presentation).

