### Recruitment

3.5

For recruitment, a study nurse in charge of enrollment will contact by phone the 217 successful participants of the third re-contact, explain the objective of the study and inquire about the interest to participate; if there is a positive response, inclusion and exclusion criteria will be verified. A list of eligible participants will be generated from the above process and sent to the person in charge of the randomization process.

After the randomization process, the study nurse will receive from the data center the list of the 150 participants selected, who will be invited to participate in the clinical trial. The nurse will call them on the pone for a face-to-face appointment where the details of the study will be informed, doubts will be clarified, and the informed consent form will be signed; a copy of the form will be given to the participant.

During that appointment, the collection of demographic and clinical data will take place, as well as a blood simple for further measurement of VD, lipid profile and glycaemia; the anthropometric nutritional, dietary and physical activity assessment will also be carried out. Once the baseline measurements are taken, the assignment to the intervention will be made in real time through software designed for the study.

Finally, the supplementation intervention will be explained in detail and the package corresponding to the participant's code will be delivered according to the process of assignment to the group (intervention/control), it will be clarified that the supplementation will last 15 weeks and then the second meeting will be scheduled to carry out again the measures taken at the beginning of the study. At the end, a third meeting will be scheduled for the delivery of results and recommendations.

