### Safety considerations

3.8

The recommendation of vitamin D in the diet for the Colombian population (males-females) is 600 IU/day, a value equivalent to a nutritional density of 40 IU/1000 Kcal. In adolescence, plasma levels decrease and needs increase; however, the recommendation is the same as for adults.^[17]^

Normally there is no toxicity by VD since it is a fat-soluble vitamin and the organism excretes it regularly. Thus, the causes of toxicity are not related to the diet or sun exposure, but to the chronic consumption of high doses of VD supplements. This is because the body regulates the amount of vitamin D produced by sun exposure and, and even fortified foods do not have large quantities of this vitamin.

Although the recommended doses are below 2000 IU, the maximum level of daily consumption which is considered tolerable is 4000 IU for people between the ages of 1 and 18, and 10,000 IU for people over the age of 19.^[18]^ On the other hand, the doses that have been documented to lead to toxicity are above 40,000 IU to 50,000 IU per day.^[16,17]^ This is considered as potentially severe condition whose symptoms are associated to secondary hypercalcemia and are mainly of a gastrointestinal nature (anorexia, nausea, vomit, constipation, diarrhea, abdominal pain) and polydipsia, polyuria, muscular weakness and fatigue, among the most relevant.^[19]^

Therefore, the supplementation with an orally administered dose of 1000 IU/day of vitamin D is completely safe for the participants and it does not have adverse effects.

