### Outcomes

3.9

*Primary outcome:* These are biochemical and anthropometric measurements that allow to respond to the purpose of the study. These include:

Total BMI. This requires taking the size in meters (m) and weight in kilograms (kg).Lipid profile: Measurements will be made of the serum levels of total cholesterol, low-density lipoprotein (LDL), high-density lipoprotein (HDL), and triglycerides.Serum levels of 25(OH) D.

*Secondary outcomes:* These are complementary measurements for the primary outcomes.

Waist-hip ratio: determines the intra-abdominal fat levels and is obtained by dividing the waist perimeter by the hip perimeter.Skin folds: These are taken for the indirect estimation of body fat percentage by means of measuring the bicipital, tricipital, abdominal, and subscapular folds.Fasting glycemia.

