### Ethics approval and consent to participate

3.12

The research will be carried out following the principles established in the Good Clinical Practice in Clinical Trials GPC/ICH. It is considered a minimum risk study according to resolution 008430 of October 4, 1993 of the Colombian Ministry of Health, since it includes the administration of a commonly used vitamin supplement with a wide therapeutic margin and for its administration the indications, doses and routes of administration established by the Institute for Drug and Food Surveillance (Invima, acronym in Spanish) are considered. The vitamin supplement is supplied by the laboratory Farma de Colombia, commercially known as Farma D, whose presentation is in soft gelatin capsules and with registration number 2017 M-0012231-R1.

The processing of personal and clinical data and biological samples will be handled according to the Habeas Data Act (Act 1266 of 2008) of the government of Colombia.

The study was reviewed and endorsed by the Technical Scientific Committee (CTC) of *Fundacion Cardiovascular de Colombia* (FCV) according to minute N°133 of May 2018 and has the approval of the Research Ethics Committee (IEC) of the FCV according to minute N°480 of July 16, 2019.

The study nurse will explain the objectives, importance, risks, benefits of the research and the confidentiality of the data. Written informed consent will be given to study participants and for participants under the age of 18 we will obtain from a parent or guardian.

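### The vitamin D exclusion covers current use only, with no look-back, so recent stoppers add noise to the 25(OH)D change and pull the paired before-after tests downward in both arms

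*Protocol article*

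**What the plan says.** Section 3.2 (Eligibility criteria) excludes "Current supplementation with VD (any presentation"). The item just before it, on steroids and hormones, has a window that runs "up to 1 month before lab sample taking". The vitamin D item has none.

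Section 3.5 (Recruitment) places the eligibility check in the first telephone call. Random selection of 150 people, a second call and the face-to-face visit with the baseline blood sample follow. No second eligibility check at that visit is described. Treatment is assigned after the baseline measurements.

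On treatment, section 3.6 (Interventions) states: "The intervention group will receive 1000 IU of VD and the control group 200 IU of VD daily for 15 weeks". Section 3.9 (Outcomes) lists "Serum levels of 25(OH) D" among the primary outcomes. Section 3.11 (Statistical analysis) tests quantitative outcomes with paired t-tests or Wilcoxon tests and mentions longitudinal methods only as something to explore.

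The other variables named in the abstract (diet, physical activity, sun exposure, tobacco, compliance) do not include earlier supplement use. Table 1 is not reproduced in the text at hand and might list more.

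**The concern.** The substance under test has a looser entry rule than steroids and hormones. Read literally, a person who stopped a daily product last week, or took one large dose last month, is not a current user and qualifies.

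Such a person's baseline 25(OH)D carries a component from the earlier intake that fades during the 15 weeks, whichever arm is assigned. It enters the change from baseline with a negative sign. Two things are at stake:

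- **Precision.** A mixture of recent stoppers and others has a more variable change in 25(OH)D.
- **The planned paired tests.** The before-after change in each arm is shifted downward. The 200 IU arm is more exposed because its expected rise is small, and a masked rise there could be misread as that dose having no effect on 25(OH)D.

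**Working it through.** **The plan's own figure.** The only calculated figure is 135 per arm, for a 20% difference in overweight, obesity and lipid alteration with 90% power and 5% alpha. The base rate is not stated. Two-sided without continuity correction, 40% versus 20% needs 109 per arm, and 109/0.8 gives 137; 41% versus 21% needs 111, and 111 × 1.2 gives 134. The figure is plausible but cannot be confirmed. It does not concern 25(OH)D, and nothing below depends on it.

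**Inputs from the protocol.** Doses of 1000 and 200 IU/day, so a contrast of 800 IU/day; 15 weeks; 75 per arm; 20% losses, leaving 75 × 0.8 = 60 per arm.

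**Assumptions, since the protocol gives no figure.** Linear first-order kinetics; half-life h of 2 to 8 weeks; earlier steady dose D; stopped t weeks before baseline; share f of recent stoppers; contrast equal to 0.5 SD of the change.

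**Step 1: one person.** In IU/day equivalents the earlier component falls over 15 weeks by D × 2^(−t/h) × (1 − 2^(−15/h)). The trial contrast builds up as 800 × (1 − 2^(−15/h)). The ratio is D × 2^(−t/h) / 800, so the conversion from IU to 25(OH)D cancels.

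| Earlier dose (IU/day) | Stopped at baseline | 4 weeks before | 12 weeks before |
|---|---|---|---|
| 600 | 0.75 | 0.19 to 0.53 | 0.01 to 0.27 |
| 1000 | 1.25 | 0.31 to 0.88 | 0.02 to 0.44 |
| 2000 | 2.5 | 0.62 to 1.77 | 0.04 to 0.88 |

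Ranges run from h = 2 to h = 8 weeks. Of the component present on stopping, a 12-week gap leaves 2^(−12/2) = 2% to 2^(−12/8) = 35%; a 4-week gap leaves 25% to 71%.

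**Step 2: mean change within an arm.** With a share f stopping at baseline, each arm's mean change drops by f × D.

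| f | D (IU/day) | Drop | Net, 200 IU arm | Net, 1000 IU arm |
|---|---|---|---|---|
| 5% | 2000 | 100 | 100 | 900 |
| 10% | 1000 | 100 | 100 | 900 |
| 10% | 2000 | 200 | 0 | 800 |
| 20% | 1000 | 200 | 0 | 800 |

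The difference between arms stays at 800 in every row.

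**Step 3: comparison between arms.** Expected bias is zero. With f = 10% and 60 per arm, the standard error of a chance imbalance, as a fraction of the contrast, is √(2 × 0.1 × 0.9/60) × D/800 = 0.055 × 1.25 = 0.07, or 0.055 × 2.5 = 0.14.

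The variance of the change, in SD² units, rises by f(1 − f)(0.5 × D/800)²:

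- D = 1000: 0.09 × 0.625² = 0.035. The standardised contrast becomes 0.5/√1.035 = 0.491.
- D = 2000: 0.09 × 1.25² = 0.141. It becomes 0.5/√1.141 = 0.468.

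Two-sided 5% power with 60 per arm goes from 78.2% to 76.8% or 72.7%. If the contrast is 0.75 SD instead, it goes from 98.4% to 97.7% or 94.7%.

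**The case against.** The strongest reply is that randomisation deals with the question that matters. Assignment follows the baseline sample, so recent stoppers are balanced in expectation and the contrast is unbiased. This stands. A reader might infer that the drift can swamp the 1000 versus 200 IU contrast, but that sets one person's fall against a difference in arm means. Even for one person it needs an earlier dose above 800 IU/day and a recent stop: within 0.6 to 2.6 weeks at 1000 IU/day, or 2.6 to 10.6 weeks at 2000 IU/day. For the mean fall to match the contrast, 800/1000 = 80% or 800/2000 = 40% of participants would have to be such users.

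Three further inferences are tempting and are not supported:

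- **That explaining the study first leads people to stop in order to qualify.** Section 3.5 does not say candidates hear the exclusion beforehand, and explaining a study before screening is ordinary practice.
- **That the missing look-back is what lets replete people in.** Section 3.2 sets no upper limit on 25(OH)D at entry, so they may enter anyway.
- **That the protocol fixes a 3-month washout.** "The daily dose selected is based on the amount required for replenishment over a period of approximately 3 months" justifies a dose. It supports a time scale for washout only indirectly.

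Prevalence is also unknown. "the administration of a commonly used vitamin supplement with a wide therapeutic margin" describes the product, not this cohort. "Although the recommended doses are below 2000 IU" makes earlier doses of 1000 IU/day or somewhat more conceivable, but does not show that anyone took them, and 2000 IU/day lies at the edge of that range.

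Finally, the article is condensed, and the operating manual or full protocol may define current use. That is possible. But the article does state a window for steroids and hormones, so the absence of one here is a feature of the criterion as published.

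**Conclusion.** The point holds in limited form. The exclusion as written admits recent stoppers and is less strict than the rule beside it. It does not bias the randomised contrast in expectation. With 10% recent users of 1000 to 2000 IU/day it costs about 1 to 5 percentage points of power for 25(OH)D, and it lowers the within-arm change by an amount equal to half or all of the rise expected on 200 IU. The paired tests named in the analysis section are therefore where the harm is greatest.

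All sizes rest on linear kinetics, steady earlier dosing, a stop right at baseline and an assumed share of users; lower doses, earlier stops or fewer users shrink them in proportion or faster. Single large doses were not modelled. It is worth correcting because the correction is cheap and, as described, earlier use could not be identified afterwards.

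**What to change.** 1. Extend the exclusion to any vitamin D-containing supplement, including multivitamins and single or intermittent high doses, taken now or within a stated look-back before the baseline blood sample. Three months is one example; by the table above, 12 weeks removes 65% to 98% of the carry-over.
2. Re-check the criterion at the baseline visit, not only in the first call.
3. Record the date and dose of last vitamin D use for everyone.
4. Make the main 25(OH)D analysis a between-arm comparison of the week-15 value adjusted for baseline, with the paired tests as description.

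**Cost.** One reworded criterion, one repeated question and two data fields. Some candidates are deferred or lost: at 10% recent users about 22 of 217, leaving 195; at 20% about 43, leaving 174, before refusals and other exclusions. If that threatens the 150 places, steps 3 and 4 without the look-back are the fallback.
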